#### Sample size considerations

Assuming a rather conservative 30% attrition rate, a *post-attrition* sample size of 54 patients or partners (18 per group) will yield 80% power to detect a difference in mean pre-post treatment FACT-SP change of 2.31 between CBMB and AC groups and between the CBMB and WLC groups, each assuming a SD of pre-post change of 2.54 (based on our pilot data) [11]. However, this trial is not designed to examine intervention efficacy, and we have not carried out any formal power calculations. In line with recommendations in the literature, we will focus on examining feasibility and descriptive analyses [45–47]. We selected the sample size of 75 dyads based on previously published psycho-oncological feasibility trials, in which the investigators typically enrolled 20–25 participants/dyads per study group [48].

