### Sample size

We will randomize 75 dyads to the CBMB intervention, AC, and WLC groups (25 dyads per group).

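### The stated 80% power for a 2.31-point FACT-SP difference does not belong to 18 per group: under a two-sided 5% t-test, power is about 76% and the difference detectable at 80% is about 2.44 (minor)

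*Protocol article*

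**What the plan says.** The protocol article randomises 75 dyads in three equal arms: "We will randomize 75 dyads to the CBMB intervention, AC, and WLC groups (25 dyads per group" (section Sample size). Under Sample size considerations it begins: "Assuming a rather conservative 30% attrition rate". It then takes a post-attrition "sample size of 54 patients or partners (18 per group" and says that this number "will yield 80% power to detect a difference in mean pre-post treatment FACT-SP change of 2.31 between CBMB and AC groups". The same claim is made for a second comparison, CBMB against wait list. The spread used for both comparisons is described as follows: "each assuming a SD of pre-post change of 2.54 (based on our pilot data".

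The sentence that follows says the trial is not designed to examine efficacy and that "we have not carried out any formal power calculations". The section then gives the actual basis for 75 dyads, which is the size of earlier psycho-oncological feasibility trials.

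**The concern.** The sentence gives every input of a two-sample power calculation except alpha and the form of the test, so it can be checked. A difference of 2.31 with an SD of 2.54 is a standardised difference of 0.909. With 18 per group that falls short of 80% power under the usual two-sided 5% test.

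The text also pulls two ways. It quotes a power to two figures and a detectable difference to two decimals, then says that no formal power calculation was made. A value such as 2.31 can hardly arise other than from such a calculation.

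What is at stake is limited. This is the document's only statement of the FACT-SP difference the trial could detect. A reader who later sets the observed between-arm differences against 2.31 would be using a benchmark that the assumed retention does not support.

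**Working it through.** **Inputs, all from Sample size considerations except where noted**
- n = 18 per group after attrition. From 25 per group (section Sample size), 25 × 0.70 = 17.5, which rounds up to 18.
- SD of pre-post change = 2.54.
- Difference in mean change = 2.31; standardised, 2.31/2.54 = 0.909.
- Stated power = 80%, for each of two pairwise comparisons.
- Alpha and test: not given with the figure. Assumed here: two-sided 0.05, two-sample t-test. Alternatives are tried below.

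**Step 1. Standard error of the difference at 18 per group**
SE = 2.54 × √(2/18) = 2.54 × 0.3333 = 0.847. Noncentrality = 2.31/0.847 = 2.73.

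**Step 2. Try to reproduce the stated 80%**
- Normal approximation: power = Φ(2.73 − 1.96) = Φ(0.77) = 77.9%.
- Exact noncentral t, df = 34: power = 75.5%.

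Neither gives 80%.

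**Step 3. Difference detectable at 80% power with 18 per group**
- Normal approximation: (1.960 + 0.842) × 0.847 = 2.37.
- Noncentral t: 2.44.

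**Step 4. Look for a reading that rescues the figure (18 per group, SD 2.54)**

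| Reading | Power at 2.31 | Detectable at 80% |
|---|---|---|
| Two-sided 0.05, t, df 34 | 75.5% | 2.44 |
| Two-sided 0.05, normal approximation | 77.9% | 2.37 |
| Two-sided 0.05, t, error pooled over three arms (df 51) | 76.3% | 2.42 |
| One-sided 0.05 or two-sided 0.10, t | 84.8% | 2.15 |
| One-sided 0.05 or two-sided 0.10, normal approximation | 86.1% | 2.11 |
| Two-sided 0.025, t | 65.0% | 2.71 |

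To reach exactly 80% at 2.31, the two-sided alpha would have to be about 0.069 (t) or 0.059 (normal approximation). Neither is a conventional level. A three-group omnibus F test with group means 2.31, 0 and 0 comes close at 78.7%, but the text describes two pairwise differences, not an omnibus test.

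**Step 5. Which n does the stated pair fit?**
Two-sided 0.05, difference 2.31, SD 2.54:

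| n per group | Power, t | Detectable at 80%, t | Power, normal | Detectable at 80%, normal |
|---|---|---|---|---|
| 18 | 75.5% | 2.442 | 77.9% | 2.372 |
| 19 | 77.9% | 2.373 | 80.04% | 2.309 |
| 20 | 80.03% | 2.309 | 82.0% | 2.250 |

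The stated pair is returned by 20 per group with the t-test, or by 19 per group with the normal approximation. It is not returned by 18 under either.

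**Step 6. A descriptive alternative**
Expected 95% confidence interval half-width for a between-arm difference in mean change, 18 per group: t(0.975, 34) × SE = 2.032 × 0.847 = 1.72 points.

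**The case against.** The strongest reply is that nothing turns on this number, and as to consequence that is right. The primary outcome is feasibility. The Statistical methods section plans means, standard deviations and confidence intervals for the quality-of-life outcomes and names no between-arm test of FACT-SP. The 75 dyads come from precedent. The disclaimer follows directly and can be read as saying that the power figure is only illustrative and did not set the sample size.

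A second reply is that the 75.5% depends on an alpha the article does not give. That also stands as a condition on the result. Under the normal approximation the shortfall is only 2.1 points and one participant per group. At two-sided 0.10 the sentence would be conservative, not optimistic. The only confidence level named in the Statistical methods section is 90%, but it is attached to the feasibility rates. None of these readings yields 80%, so the stated combination remains wrong; calling it optimistic assumes two-sided 5%.

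A reader might infer more than the document supports:
- **That 2.31 will mis-size the larger trial.** The Discussion says that trial will be sized on clinically meaningful changes in the outcomes. Nothing hands on 2.31, 2.54 or 80%.
- **That two comparisons require a multiplicity adjustment.** The outcome analyses are descriptive and the sentence speaks of each comparison separately. The two-sided 0.025 row above only shows that this level does not recover 80%.
- **That the unstated alpha is itself a fault.** A condensed article may leave it to the full protocol or analysis plan.
- **That the SD of 2.54 is too small.** It is attributed to pilot data, and the article gives no other value to set against it.
- **That the figure was left over from a 20% attrition assumption,** since 25 × 0.80 = 20. This is possible, but the article does not say so.

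**Conclusion.** Wrong as written, and minor. With 18 per group and an SD of change of 2.54, a two-sided 5% two-sample t-test has about 75.5% power for a difference of 2.31 (77.9% by normal approximation). The difference detectable at 80% is about 2.44 (2.37 by normal approximation). The overstatement is therefore about 2 to 4.5 percentage points of power, or 0.06 to 0.13 points on the detectable difference.

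The sizes rest on the assumed two-sided 5% level and on the article's own n and SD. That 80%, 2.31, 2.54 and 18 do not fit together holds at every conventional alpha tried. The disclaimer limits how far a reader should lean on the figure but does not make it right, and the two sentences need to be reconciled.

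**What to change.** Choose one of two edits in Sample size considerations:

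1. Restate the claim: 18 per group gives 80% power (t-test, two-sided alpha 0.05, each comparison unadjusted) for a difference of 2.44 if the SD of change is 2.54; power for 2.31 is about 76%.
2. Delete the power claim and give the expected precision instead: a 95% confidence interval half-width of about 1.72 points for a between-arm difference in mean FACT-SP change with 18 per group. This suits the descriptive second aim better.

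With the first edit, also change the disclaimer so that it says the sample size was not chosen by a power calculation and that the figure is for orientation only. With the second, the disclaimer can stand as it is.

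The cost is one or two sentences of wording and, under the first edit, a slightly less favourable figure. The 75 dyads, the feasibility criteria and the planned analyses do not change.

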## Discussion

This study will provide the necessary evidence of the feasibility of an RCT of a CBMB intervention for couples coping with mNSCLC, a vulnerable yet understudied population, using videoconference delivery. Given the paucity of existing RCTs of interventions for behavioral supportive care interventions for patients with advanced cancer, findings of this research will be of interest to other researchers working in this area or wanting to examine recruitment for other technology-based intervention studies in similar populations.

We acknowledge that the proposed study sample excludes nonromantic family caregivers (e.g., adult children) and patients with other forms of aggressive lung cancer, such as extensive small-cell lung cancer. Given that this is a small trial, we believe that a rather homogenous sample is justifiable at this stage of development. However, if our feasibility criteria are not met, we will expand the trial to other family caregivers and types of lung cancer. Once the trial’s feasibility is established to inform a future larger study, we will design that RCT with a sample size that will be informed by clinically meaningful changes in study outcomes. We will present findings of this feasibility trial at national and international behavioral medicine and supportive care conferences and submit them for publication in peer-reviewed journals.

### Trial status

Participant recruitment started on March 15, 2017 and is expected to be finished by July 2018.

## Abbreviations

AC: Active control
CBMB: Couple-based mind-body
ECOG: Eastern Cooperative Oncology Group
FACT-SP: Functional Assessment of Cancer Therapy - Spiritual Well-Being Scale
mNSCLC: Metastatic non-small cell lung cancer
NCCN: National Comprehensive Cancer Network
QOL: Quality of life
RCT: Randomized controlled trial
WLC: Wait list control
